### Randomization

Allocation is conducted by non-study personnel on a per-patient basis using a permuted block algorithm accessible via a computer program with full-entry tracking. Participants are randomly allocated with a 1:1 ratio to either XR-NTX or BP-NLX independent of site, setting (clinic or criminal justice) or gender. When a study staff member contacts allocation staff for inclusion and randomization, inclusion criteria are verified before the patient is formally included into the database and allocated to one of the two medication groups. Group allocation is communicated openly to study staff via telephone, who are then free to communicate the results of the allocation procedure to patient and clinical staff in an open-label manner.

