#### Outcomes & instruments

Urine Drug Test (UDT) data will be analyzed in accordance with recent Cochrane specifications as either a) proportion of total number of UDTs without illicit opioids or b) number of UDTs negative for illicit opioids received from each patient in each group during the 12-week randomized period [37].

Retention in treatment is defined in two ways: Number of days (of maximum 84 days) receiving effective pharmacological treatment, and number of patients completing the study at Week 12.

At baseline and every 4 weeks, patients undergo a structured interview and a selection of patient-reported outcomes: The European version of the Addiction Severity Index (the Europ-ASI) [38, 39] comprises drug and alcohol use, physical and mental health, work, education, social relations, and criminal behavior. The Europ-ASI is used for the second main drug use outcome measure, the number of days of abstinence from illicit opioid use in the 28 days preceding each interview for a total (maximum) of 84 days. To increase accuracy of responses relative to the Europ-ASI standard, timeline follow-back is used: a technique of backtracking and questioning about use and abstinence to obtain as accurate an estimate as possible of total number of days’ use of a specific substance in the 28-day follow-up period [40].

In addition to the primary outcomes, we explore secondary outcomes of importance to recovery: Number of patients fulfilling MINI [36] (DSM-IV) criteria for dependence on illicit opioids (exempting the 12-month criterion). The Addiction Severity Index administered every 4th week also records information on the use/abuse of alcohol, amphetamines, cannabis, sedatives (e.g. benzodiazepines), as well as other illicit substances (e.g. LSD, MDMA, GHB), and poly-drug use; days of injecting drug use; any overdoses (non-lethal) and hospitalizations in somatic or psychiatric health care; workdays and days engaged in illegal activities; number of days with conflicts in close relations, days physical and mental illness.

Craving for heroin is assessed using a 0–10 Visual analogue scale (VAS) on two questions: ‘I need heroin’ where ‘0’ signifies ‘Strongly disagree’ and 10 ‘Strongly agree’; and ‘How much have you been bothered by thinking about opioids or their use in the past 4 weeks?’ with 0 indicating ‘not at all’ and 100 ‘constantly’.

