### Statistical analyses

Statistical analyses on the randomized part of the study will be conducted by a non-study statistician on a final RCT data set in which the two study medications is masked as ‘Rx A’ and ‘Rx B’; any obvious characteristics of the two comparison medications will also be censored before data are made available for analysis. For between- group comparisons and to control for the effect of baseline characteristics, we will use a General Linear Mixed Models (GLMM) approach containing factors for treatment group, sex, and sex-by- treatment interaction, and with age, duration of opioid dependence, and duration of last pre-study inpatient detoxification as covariates. For outcomes violating the normality assumption, a General Alinear Mixed Models (GAMM) approach will be used. Regular statistics (e.g. ANOVA, linear regression) may be utilized if the arguments for using GLMM or GAMM over legacy analysis types are considered to provide limited benefit. Retention will be assessed with Kaplan-Meier curves and a log-rank test. Adverse events will be compared using Fisher’s exact test. The primary endpoints are tested with a two-sided α = 0.05. Where relevant, *p* values will be adjusted for multiplicity using the Bonferroni-Holm method to preserve family-wise type 1 error at 0.05. Once the statistician concludes data analysis of the RCT phase, study management will be able to access the final dataset.

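### The between-group model keeps a sex-by-treatment interaction that answers no stated question, names no treatment contrast, and omits baseline illicit opioid use

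*Protocol article*

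**What the plan says.** The Statistical analyses section of the protocol article gives the model's purpose as between-group comparison and "to control for the effect of baseline characteristics". The model is described as "containing factors for treatment group, sex, and sex-by- treatment interaction, and with age, duration of opioid dependence"; the only other covariate is how long the most recent detoxification before the study lasted. Baseline illicit opioid use is not among these terms, and no contrast is named as the treatment test. The same section permits simpler methods: "Regular statistics (e.g. ANOVA, linear regression) may be utilized" where a mixed model is thought to add little. Retention, one of the primary outcomes, has its own method: "Retention will be assessed with Kaplan-Meier curves and a log-rank test".

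Four other places bear on the point:

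- **Outcomes & instruments:** at baseline and every 4 weeks, "patients undergo a structured interview and a selection of patient-reported outcomes". The interview is the Europ-ASI, which supplies the self-reported illicit opioid days.
- **Analysis sets:** missing assessments are filled with the last attended follow-up or, if there was none, with the inclusion data. Inclusion data may be corrected for days in a controlled environment.
- **Randomization:** allocation is 1:1 and "independent of site, setting (clinic or criminal justice) or gender".
- **Research questions and hypotheses:** superiority and non-superiority hypotheses are stated for the two treatments. None concerns sex.

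**The concern.** Once a sex-by-treatment term is in the model, there is no longer a single treatment parameter. A dummy-coded coefficient is the effect in the reference sex. A type III test addresses the simple average of the male and female effects, whatever their numbers. The article does not say which is meant. If the sexes are unequal in number, either one is less precise than the main-effects estimate, and that cost is paid for a question the trial does not pose.

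The omission of baseline use goes the other way: a likely strong predictor is collected but not used. Entrants range from patients stable on daily buprenorphine to users of illicit heroin (Pre-randomization tapering of opioid agonists), so baseline illicit use probably varies widely. For a patient without follow-up, the analysed self-report value may be the baseline value itself, so a chance imbalance in baseline use would pass straight into the comparison. At stake are the precision and clarity of the urine-test and self-report comparisons.

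**Working it through.** **Inputs from the article** (Determination of sample size; Statistical analyses): means of 7 and 4 negative samples of 12, difference 3, SD 3, two-sided alpha 0.05, power 90%, planned 90 per arm.

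**Assumptions, not in the article:** share of women f = 0.20 to 0.40, equal in both arms; baseline-outcome correlation r = 0.3 to 0.5.

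**1. The plan's own figure.** n per arm = 2 × (1.960 + 1.282)² × (3/3)² = 21.01, rounded up to 22. The article states 17, which is close to the t-based result for 80% power (16.7). This mismatch is a separate matter and neither supports nor weakens the present point. The working below uses the planned 90 per arm.

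**2. Cost of the interaction.** With n per arm and residual SD σ, the main-effects treatment variance is 2σ²/n. The effect in women has variance 2σ²/(nf), and the effect in men 2σ²/(n(1−f)). Their simple average has variance ¼ × [2σ²/(nf) + 2σ²/(n(1−f))], which is the main-effects variance times V = 1/(4f(1−f)).

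- A test with 90% power without the interaction has power Φ(3.242/√V − 1.960) with it.
- At 90 per arm and SD 3, the main-effects standard error is 3 × √(2/90) = 0.447, so the 95% half-width is 0.88 samples. With the interaction it is 0.88 × √V.
- Power at the planned difference is Φ(√(90/(2V)) − 1.960), because difference and SD are equal.

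| Women | V | √V | 90% power becomes | Half-width (samples) | Power at difference 3 |
|---|---|---|---|---|---|
| 20% | 1.56 | 1.25 | 74% | 1.10 | above 99% |
| 30% | 1.19 | 1.09 | 84% | 0.96 | above 99% |
| 40% | 1.04 | 1.02 | 89% | 0.89 | above 99% |

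At 50% women V is 1.00 and the equal-weighted test costs nothing.

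**3. If the raw dummy-coded coefficient is read instead.** Its variance factor is 1/(1−f) with men as reference and 1/f with women as reference. At the planned difference, power stays above 99% with men as reference. With women as reference it is 85% at f = 0.20 (90/5 = 18 per arm; √(18/2) − 1.960 = 1.04) and 99% at f = 0.40.

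**4. Is the test itself tied to coding?** One data set was simulated with 180 patients, 30% women, SD 3 and a built-in sex difference in effect. Without the interaction the treatment estimate was 0.69 (p = 0.086). With it, the raw coefficient was 1.05 (p = 0.029) with men as reference and −0.14 (p = 0.85) with women as reference. The type III test gave p = 0.299 whichever sex was coded first. So the raw coefficient depends on coding and the type III test does not, but the latter tests a different quantity from the main-effects model.

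**5. Gain from baseline adjustment.** Residual variance is multiplied by 1 − r².

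- r = 0.3: 1 − 0.09 = 0.91, a 9% cut; 90 per arm works like 90/0.91 = 99, and 80% power becomes 84%.
- r = 0.5: 1 − 0.25 = 0.75, a 25% cut; 90 per arm works like 90/0.75 = 120, and 80% power becomes 90%.

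**The case against.** The strongest reply is that this hardly matters at the planned effect. Power for the equal-weighted test stays above 99%, and retention, whose non-superiority calculation gives the larger of the two minimum sample sizes, is tested by log-rank with no sex term. The article calls the study exploratory, permits ANOVA or regression instead, and does not label this model as primary. A prespecified sex interaction in an exploratory trial is not a mistake in itself. All of this stands, and it limits the size of the point.

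The article is also condensed. It describes no random effects, and baseline might enter as a repeated measurement in a fuller document. That is possible. But the text gives an explicit list of terms whose stated purpose is control of baseline characteristics, and a plan that follows it would inherit both features.

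Omitting a prognostic covariate costs efficiency and does not bias a randomised comparison. That stands too. So does the remark that the 12-week urine count has no direct baseline equivalent, and that baseline days may be distorted by time in detoxification.

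Three stronger readings are tempting and are not supported:

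- **That the result hangs on a software default.** This is true only of a raw dummy-coded coefficient. A type III or marginal test does not change with the reference sex, and the article speaks of factors.
- **That power collapses.** This needs women as the reference level and the raw coefficient read as the overall effect, which nothing in the article suggests. Even then, power at the planned difference is about 85% in the worst case examined.
- **That leaving out site is an error.** Allocation was not stratified by site, so the test is valid without it. No between-site variance is given, and the random effects are not described. Adding site is a preference.

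**Conclusion.** The point holds as one of efficiency and clarity for the urine-test and self-report comparisons. The listed model contains an interaction that serves no stated hypothesis, leaves the treatment contrast open, and omits the collected baseline value of its self-report primary outcome.

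The interaction makes the interval for the equal-weighted effect 2% to 25% wider, if 40% to 20% of patients are women. Omitting baseline use forgoes a 9% to 25% reduction in residual variance, if the correlation is 0.3 to 0.5. The article gives neither the share of women nor the correlation. If the sexes are equally represented, the first cost vanishes under the equal-weighted test.

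The superiority test at the planned difference is not endangered. The loss bears on smaller effects, on secondary outcomes, and on how tightly a finding of equal effectiveness can be stated. The planned analysis is not invalid or biased on this account.

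**What to change.** Make the main analysis a main-effects model with treatment, sex, age, duration of dependence and detoxification duration, plus the baseline value of the outcome where one exists. Name the treatment effect in that model as the tested contrast.

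For self-reported use, the baseline value is the Europ-ASI illicit opioid days, corrected for controlled-environment days as the Analysis sets section foresees. The same variable can serve as a proxy for the urine outcome. Fix its definition before the masked data set goes to the statistician. Report sex-by-treatment as a separate exploratory test.

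The cost is a change of wording and one more covariate, with no new data collection. There are two limits. Baseline days may still reflect time in a controlled environment, and the proxy may predict the urine count less well than it predicts self-reported days. Baseline adjustment also does not make carrying inclusion data forward a sound imputation; it only keeps a chance baseline imbalance from passing unadjusted into the comparison.

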### Research questions and hypotheses

The main research question is whether 4-week XR-NTX will be more effective than–or equally effective to a current standard treatment–daily BP-NLX–on primary and secondary outcomes during or at the end of the 12-Week study.

As an exploratory study with both non-superiority and superiority as plausible scenarios [34] there are two sets of hypotheses for this RCT:

XR-NTX will influence primary and secondary outcomes to be either:statistically superior to assignment to the current standard treatment, ART with daily BP-NLX orstatistically non-superior to ART with daily BP-NLX.

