#### Determination of sample size

In compliance with current recommendations for non-superiority trials [34], a minimum sample size has been estimated for two scenarios:

The superiority scenario assumes that XR-NTX participants will have opioid-negative samples on a mean of 7 out of the total 12 (7/12 or 0.58) samples, while participants receiving buprenorphine-naloxone will display a mean of 4 opioid-negative samples (4/12 or 0.33). With a 95 % significance level (*p* < 0.05) and a standard deviation of 3 in both medication groups, and power (beta) set to 90 %, a sample size of 17 patients/medication arm or *n* = 34 total is estimated to be sufficient for analysis. The estimated frequency of opioid use in each group is based on data from Norwegian patients receiving sustained release naltrexone [22] or on the frequency of illicit opioid use during buprenorphine maintenance in the Norwegian national ART program.

In the non-superiority scenario, using a beta of 90 %, we assume that both groups will retain 70 % of their participants at the end of Week 12 and set 20 % as the non-superiority margin; this yields a minimum sample size of *n* = 58 in each group/*n* = 116 total.

Based on the sample size calculations and the risk of dropout of a significant proportion of participants, we have set the recruitment target for *n* = 180 total, or *n* = 90 for each medication group. This will be facilitated by characteristics of design (few exclusion criteria, open-label allocation, outpatient data collection often coinciding with medication and counseling), prioritization of amount–and types of data collected. Information about the study will be distributed at clinical sites as well as outreach -, housing- and criminal justice facilities and the internet; these efforts are anticipated to attract the initial *n* = 30 patients whose presence in the larger community of opioid users will be sufficiently inform more potential participants to contact study staff for information.

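### The 20% retention margin that set the larger minimum sample size has no stated test: the only retention analysis named is a log-rank test of difference

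*Protocol article*

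**What the plan says.** Under Research questions and hypotheses, the protocol article asks whether XR-NTX is more effective than BP-NLX or "equally effective to a current standard treatment". It sets out two hypotheses, one of superiority and one that it calls non-superiority.

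Under Determination of sample size, the second hypothesis is tied to retention: "we assume that both groups will retain 70 % of their participants at the end of Week 12", and the authors "set 20 % as the non-superiority margin". Power is 90% (the text writes beta). The result is 58 per group, 116 in total, against 34 in total for the superiority scenario on urine tests. The target is then set at 180, or 90 per group, to allow for dropout.

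Under Statistical analyses, the retention analysis is named: "Retention will be assessed with Kaplan-Meier curves and a log-rank test". The same paragraph says: "The primary endpoints are tested with a two-sided α = 0.05". P values are, where relevant, "adjusted for multiplicity using the Bonferroni-Holm method to preserve family-wise type 1 error at 0.05".

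The margin appears only in the sample-size section. No confidence interval, shifted null hypothesis or decision rule refers to it.

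**The concern.** The article fixes two things that do not fit together: a margin that produces the larger minimum size, and a test that cannot use a margin. The log-rank null hypothesis is that the curves are equal. Rejecting it shows a difference; failing to reject it shows nothing about how large a difference remains possible. The mixed-model, ANOVA and regression options in the same paragraph are also described without a margin.

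Retention is a primary outcome, and equal effectiveness is one of the two answers the trial sets out to give. If no rule for that answer is fixed in advance, the natural fallback is to report a non-significant log-rank test as equal retention. That would treat absence of evidence as evidence of equality.

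**Working it through.** **Inputs from the article.** Retention 70% in both arms; margin 20%; power 90%; 58 per arm (minimum) and 90 per arm (target); 1:1 allocation; two-sided 0.05.

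**Assumptions.** The margin is in absolute percentage points and concerns XR-NTX being worse, so retention at the margin is 70% against 50%. All 90 per arm are analysed; leaving treatment is itself the event on this outcome.

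**1. The article's own figure.** The usual formula for a margin test of two proportions is n per arm = (z₁₋α + z_power)² × 2p(1−p) / margin².
- One-sided 2.5%: (1.960 + 1.282)² × 0.42 / 0.04 = 10.51 × 10.5 → 111.
- One-sided 5%: (1.645 + 1.282)² × 10.5 = 8.56 × 10.5 → 90.

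Neither gives 58. At 80% power the formula gives 83 and 65. The figure of 58 is therefore not reproduced from its stated inputs. That is a separate matter, but it bears on the power quoted in step 4.

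**2. Chance of a non-significant two-sided 5% test when XR-NTX is exactly at the margin (70% against 50%).**

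*Difference of proportions, 90 per arm.* SE under the null = √(2 × 0.6 × 0.4 / 90) = 0.0730; SE under the alternative = √((0.21 + 0.25) / 90) = 0.0715. Power = Φ((0.20 − 1.96 × 0.0730) / 0.0715) = Φ(0.795) = 0.787, so 21.3% are non-significant.

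*Log-rank by Schoenfeld's formula, 90 per arm.* Hazard ratio = ln 0.5 / ln 0.7 = 1.94; events = 90 × (0.3 + 0.5) = 72. Power = Φ(√72 / 2 × ln 1.94 − 1.96) = 0.805, so 19.5% are non-significant.

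| Method | 90 per arm | 58 per arm |
|---|---|---|
| Difference of proportions, formula | 21.3% | 40.4% |
| Exact binomial | 20.7% | 40.8% |
| Schoenfeld | 19.5% | 38.1% |
| Simulated log-rank, 5,000 runs (constant hazard, early dropout, 28-day grouped times) | 19.8–21.2% | 38.8–39.5% |

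With a first Holm step at 0.025 or 0.0167, the 21.3% becomes 31% or 36%.

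**3. Error of a rule that does use the margin, same truth, 90 per arm.** The lower limit of a two-sided 95% CI lies above −20 points in 2.55% of trials (exact). A one-sided 5% rule passes in 5.2%.

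**4. Power of the margin rule when both arms truly retain 70%.** Power = Φ(√(0.04n / 0.42) − z₁₋α).
- 90 per arm, one-sided 2.5%: Φ(2.928 − 1.960) = 83%.
- 90 per arm, one-sided 5%: Φ(2.928 − 1.645) = 90%.
- 58 per arm, one-sided 2.5%: Φ(2.350 − 1.960) = 65%.

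**5. Can the two rules collide the other way?** At 90 per arm the 95% half-width near 70% retention is 1.96 × √(0.42 / 90) = 13.4 points. Passing the margin needs an observed loss below about 20 − 13.4 = 6.6 points; a significant loss needs more than about 13.4. The two ranges do not meet. The computed probability of both in one trial is below 1e-8.

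**The case against.** The strongest reply is that this is a condensed article, that the full protocol and any SAP are not shown, and that comparing an interval with a margin is the kind of detail left to them. The article also does not say that the log-rank test is the only retention analysis. That would answer a complaint of missing detail. It does not answer this one, because the article does name the retention analysis and the alpha, and what it names cannot address the margin it was sized on.

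A second reply is that retention has two definitions, days in treatment and number completing Week 12. The log-rank test may serve the first and the margin the second. This is possible, but then the second has no named test other than general comparisons without a margin. The conclusion is the same.

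A third reply is that Kaplan-Meier estimates carry standard errors, so a Week-12 difference with a CI can be derived from a method already named. This stands. The gap is in the rule, not in the available quantities, and the fix can use those estimates.

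The article also calls the trial exploratory. It nevertheless sets a margin, a power, an alpha and family-wise error control.

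Two stronger readings are tempting and are not supported:
- A reader might infer that the plan will declare equality from p > 0.05. No such rule is written. It is only the route left open.
- A reader might infer that a significant log-rank test could condemn XR-NTX while its CI lies inside the margin. At 90 per arm this practically never happens (step 5), and the article has no rule that rejects XR-NTX.

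**Conclusion.** The point holds as a mismatch between two elements the article fixes: the scenario behind the larger minimum size has no stated test.

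The size of the problem is conditional. If equal effectiveness were read from a non-significant test, a true 20-point loss would be accepted as equal in about 21% of trials at 90 per arm and about 38–41% at 58. A rule based on the margin would err in about 2.5% (two-sided 95% CI) or 5% (one-sided 5%). The contrast therefore does not depend on which alpha was intended.

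These figures rest on the assumptions listed above. The article does not state the direction or scale of the margin, nor the alpha for a margin test, and its term non-superiority leaves the direction open. Reading it as not worse fits the equal-effectiveness question and the equal assumed rates. Fewer analysed patients or a Holm-adjusted alpha would push the 21% upward.

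**What to change.** In the Statistical analyses section:
- State the direction and scale of the 20% margin.
- Make the test of the not-worse hypothesis the Week-12 retention difference, XR-NTX minus BP-NLX, in all randomised patients, with its two-sided 95% CI. Conclude not worse only if the lower limit is above −20 points. The difference may come from proportions (for example a Newcombe or Miettinen-Nurminen interval) or from the Kaplan-Meier estimates.
- Keep the log-rank test for difference or superiority, and say that a non-significant result is not evidence of equal retention.

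This takes a few sentences and no new data, and should be settled before the masked dataset is analysed. It has two costs. Equality becomes harder to claim: at a true XR-NTX retention of 60%, simulation at 90 per arm gave a non-significant log-rank test in 69% of trials but a passed margin in only 28%. And the stated 90% power is not met: it is about 83% at 90 per arm and 65% at 58, with 111 per arm needed for 90%. The sample-size section must either restate the power or tie it to a one-sided 5% rule, which gives about 90% at 90 per arm with a false-acceptance rate of about 5%.

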## Abstract

**Background:**

Current guidelines for opioid dependence recommend daily maintenance of physical dependence with methadone or buprenorphine, and discourage abstinence due to the high risk of relapse and overdose. Extended-release formulations of the opioid antagonist naltrexone (XR-NTX) block heroin and other opioid agonists competitively for around 4 weeks per administration. XR-NTX thus enables opioid users to experience abstinence from opioid agonists with greatly reduced risk of overdose compared to medication-free abstinence. While XR-NTX has shown promise compared to placebo and daily naltrexone tablets, there is limited information on long-term safety and its performance compared to daily maintenance treatment.

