## Methods/Design

### Study design

This is a 12-week open-label randomized-controlled trial comparing 4-week intramuscular injections of extended release naltrexone (XR-NTX) to a currently recommended treatment for opioid addiction, daily buprenorphine-naloxone (BP-NLX). As this is he first RCT comparing these two medications, we consider the scientific approach to be exploratory.

For ethical reasons (see below) study medication (XR-NTX) will not be terminated upon RCT completion, but will be available for an additional 36 weeks (48 weeks total observation time). This will produce long-term data clinical safety and effectiveness of chronic naltrexone treatment. Registry data collection of mortality, morbidity, criminal justice and prescription records will take place before, during and after the prospective data observation in order to provide additional information on the volunteers and long-term effects of XR-NTX medication.

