#### Regulatory approvals, data–and safety monitoring

The Common Terminology Criteria for Adverse Events (CTCAE) version 4 is used to classify adverse events at follow-up. Any event requiring medical intervention is registered (CTCAE level 2 or above). Medication-related Severe Adverse Events (SAEs) and Sudden Unexpected Severe Adverse Reactions (SUSARS) are reported to the Norwegian Medicines Agency (European Medicines Agency) and to the study drug manufacturers (Alkermes, Inc. and Reckitt-Benckiser, Inc.) within two working days. No interim analyses are planned, but the Sponsor (the University of Oslo, Norway) as well as regulatory authorities may stop recruitment and further medication with study medication in the case of an emergency, e.g. an unusual accumulation of SAEs or SUSARs attributable to study medication.

As all participants are enrolled in a local ART clinic, ART services are assigned the legal responsibility for monitoring of everyday safety of the patient with the option of discontinuing patients from ART if necessary (and thus from study participation). In addition, a local data and safety monitoring committee consisting of site investigator, site coordinator, and a representative of the clinical monitoring service are responsible for assessing data quality and safety at each study site. National management consisting of LT, and NK, conducts additional supervision, provide training and guidance and assess compliance with the study protocol of all serious adverse events. As this is an investigator-initiated trial, there are no competing interests and the sponsor, the University of Oslo, Norway, is represented by the National PI (LT).

All relevant study personnel are trained in ICH-GCP and CTCAE event registration. All participants are insured against SAEs attributable to study drug (XR-NTX) occurring during or after participation via the Sponsor’s membership in the Norwegian Drug Liability Association.

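### The Fisher's exact comparison of adverse events ignores observation time, so unequal dropout between arms can bias it in either direction

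*Protocol article*

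**What the plan says.** The Statistical analyses section gives adverse events one sentence: "Adverse events will be compared using Fisher’s exact test". Retention, in the same section, gets Kaplan-Meier curves and a log-rank test.

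The Regulatory approvals, data and safety monitoring section explains how events are captured: "The Common Terminology Criteria for Adverse Events (CTCAE) version 4 is used to classify adverse events at follow-up". Events needing medical intervention (CTCAE level 2 or above) are registered.

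The Determination of sample size section assumes 70% retention at Week 12 in both groups. The sentence that sets the target ("we have set the recruitment target for *n* = 180 total, or *n* = 90 for each medication group") names dropout as a reason for it. The Study medications section has the two arms enter treatment differently after randomisation. Naltrexone patients continue tapering, spend a minimum period without opioid agonists and have a naloxone challenge before the first injection. Buprenorphine-naloxone patients are inducted directly.

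**The concern.** A comparison of proportions with an event is fair when both arms are watched for equally long. Here the document gives reasons to doubt that. About 30% of patients are expected to be lost by Week 12, induction differs by arm after randomisation, and the Discontinuation section defines non-adherence differently for each drug. Because events are classified at follow-up, a patient who stops attending has less chance of having one recorded.

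The arm that loses patients sooner then looks safer than it is. If that arm carries the higher risk, a real excess is diluted. If the other arm loses more, the excess is exaggerated. If the two risks are equal, a difference appears that does not exist. The plan handles time for retention but not for harms subject to the same dropout.

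**Working it through.** **Inputs from the document.** 90 patients per arm, 1:1 allocation, 84 days. Two-sided 5% is stated for the primary endpoints only and is assumed here for adverse events. The article gives no adverse-event rate and no power for the safety comparison, so there is no figure of its own to reproduce.

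**Assumptions.** Event rates and the dropout split are illustrative. Event and dropout times are exponential and independent, and adverse-event observation ends at dropout.

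**Recorded risk.** With 84 days as the time unit, full-observation risk r and dropout proportion q, the event hazard is h = −ln(1−r) and the dropout hazard is d = −ln(1−q). The chance that a patient has a recorded event is

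h/(h+d) × [1 − (1−r)(1−q)].

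- Lower-risk arm, r = 10%, q = 20%: h = 0.105, d = 0.223; 0.321 × (1 − 0.9×0.8) = 0.321 × 0.28 = 9.0%.
- Higher-risk arm, r = 20%, q = 50%: h = 0.223, d = 0.693; 0.244 × (1 − 0.8×0.5) = 0.244 × 0.60 = 14.6%.
- Crude risk ratio: 0.1461/0.0898 = 1.63 (about 1.65 by simulation) instead of 2.0. Crude risk difference: 5.6 points instead of 10.

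**Rate ratio on the same data.** Mean observed time is [1 − (1−r)(1−q)]/(h+d): 0.28/0.3285 = 0.852 and 0.60/0.9163 = 0.655. The rate ratio is (0.1461/0.655)/(0.0898/0.852) = 2.12, equal to the true hazard ratio 0.223/0.105 = 2.12.

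**Power.** Fisher: the product of the two binomial probabilities, summed over all 91 × 91 tables with p ≤ 0.05. Rate comparison: simulated exact conditional test, splitting the total events by share of patient-time.

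| Dropout, lower-risk / higher-risk arm | Crude risk ratio | Fisher power | Exact rate test |
|---|---|---|---|
| none | 2.0 | 40% | 43% |
| 30% / 30% | 2.0 | 33% | 37% |
| 20% / 50% | 1.63 | 16% (17% by simulation) | 37–38% |
| 50% / 20% | 2.48 | 52% | 35% |

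The last row uses the same formula: recorded risks 7.3% and 18.0%. There Fisher's extra power comes from an exaggerated effect.

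**No true difference, dropout 20% / 50%.** At 20% risk in both arms the recorded risks are 18.0% and 14.6% (ratio 0.81), and Fisher rejects 6.5% of the time. At 30% it rejects 9%, and at 40% about 12%. At 10% risk it rejects 4%, because the test is conservative with few events. The exact rate test stays at 4–5% throughout.

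**A milder case.** Suppose mean exposure is 80% in the comparator and 60% in the other arm, with a hazard ratio of 2 from a 10% risk. The recorded risks are 1 − exp(−0.105×0.8) = 8.1% and 1 − exp(−0.105×2×0.6) = 11.9%. The crude ratio is 1.47 and Fisher power is 9%. With 80% exposure in both arms, power would be 27%.

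**The case against.** The strongest reply is that this is a condensed article without its full protocol or analysis plan. Fisher's test for adverse-event counts is standard, and effect estimates, intervals and table layouts are commonly left to the later document. That stands: missing confidence intervals alone would be no finding. But the article does fix the test, and an analysis plan that follows it inherits a comparison blind to observation time.

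Second, the article assumes equal retention, so the 20% / 50% split is invented. That also stands, and with equal dropout Fisher's test loses little. The 70% refers to retention; if patients who stop treatment are still assessed for events, the bias shrinks.

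Third, a rate ratio has its own assumption, that dropout is unrelated to harm, which may fail in this population. It reduces the problem and does not cure it.

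Two stronger readings are not supported:

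- A reader might infer that Fisher's test is the only between-arm safety comparison. Non-fatal overdoses and hospitalisations are secondary outcomes under the general between-group model, and registry data add events, including for patients who discontinue naltrexone.
- A reader might infer that a doubling of harm would usually be reported as no difference. At 90 per arm, power for a doubling is 17% for 5% vs 10% and 40% for 10% vs 20%, but 62% for 15% vs 30% and 80% for 20% vs 40%. It passes 50% at a comparator risk of about 12%, and the article states no rate. Nor does it say that a non-significant result will be read as safety. Low power comes from sample size and rare events, and an interval would not raise it.

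**Conclusion.** The point holds in a limited form. The stated test ignores time at risk in a trial whose own design makes unequal time at risk plausible, and the resulting bias can go either way. Under the assumed 10% vs 20% risks and 20% / 50% dropout, a true doubling shrinks to a crude ratio of about 1.6, and power falls to about 16–17% against 37–38% for a rate comparison. Reversing the dropout inflates the ratio to about 2.5. These figures rest on assumed event rates, an assumed dropout split, and loss from the study meaning loss of event recording. The article calls the trial exploratory, and the change concerns analysis and reporting, not design.

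**What to change.** Amend the adverse-event sentence in Statistical analyses to say in substance: for adverse events of CTCAE grade 2 or above, and for serious adverse events, report by randomised arm over the 84 days the number of events, the number of patients with an event and the patient-days observed. Give an incidence-rate ratio (exact, or Poisson or negative binomial with log observation time as offset) and a risk difference, each with a 95% confidence interval. Keep Fisher's p-values as descriptive. A crude risk difference shares the fault described here, so either take it from Kaplan-Meier estimates at day 84 or present it beside the patient-days.

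The cost is one or two sentences and a few table columns. It needs no new patients and should need little beyond event records and follow-up dates. The intervals will be wide, and the report should say that the rate ratio assumes dropout is unrelated to harm.
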